#### School staff outcomes

Descriptive statistics (mean, SD, median) will be used to gauge the level of confidence and perceived ability at baseline and post-intervention. Paired *t*-test will be used to test if there is a significant change between baseline and follow-up. The general linear model will also be used to examine if the changes are related to possible covariates such as baseline levels and previous training.

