## Methods

### Aims

The primary aim of this study is to examine whether or not participation in the Reframe-IT program leads to reduced: 1) suicidal ideation. Additional aims are to examine its impact on: 2) symptoms of depression, and 3) levels of hopelessness, among participating students, and to determine if it leads to: 4) increased confidence 5) increases in perceived skill, and 6) changes in practice among school wellbeing staff (in particular with regard to their use of Internet-based programs and resources with at-risk students).

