### Study design

The student-related aims listed above will be addressed via a randomised-controlled trial. The study has a staggered two-year recruitment phase and involves the delivery of eight modules of CBT delivered over a 10-week intervention period. Students are followed up post intervention and again 12 weeks later. The study has been designed in order that the CONSORT guidelines [40] can be met when reporting the trial.

The aims related to school staff will be assessed using a pre-test/post-test design.

The study team comprises a project coordinator (JR), a research therapist (SH); two research assistants; a clinical psychologist (SB), and a statistician ([name]).

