#### School staff outcomes

These will be measured using a specifically designed questionnaire, based on those previously used by this research team [58]. This will be administered prior to the beginning of each school’s involvement in the study and at the end of the intervention period. If a staff member leaves the school before the end of the study they will be asked to complete the questionnaire before their departure. The questionnaire will assess attitudes, confidence; perceived skill and changes in practice.

All outcome data will de-identified and stored on a password-protected database located on a secure server housed by Orygen Youth Health Research Centre.

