### Effect size and statistical power

The primary outcome of interest is changes in suicidal ideation from baseline measured at 10 and 22 weeks. This will be measured by the SIQ. No previous studies have tested the effects of an Internet-based CBT intervention on suicidal ideation, however one previous study [59] has reported moderate to large effect sizes in terms of reduced suicidal ideation, for face-to-face CBT among young people. If we assume that alpha is set at 0.05 and power at 0.80, then a sample size of 58 is required for each of the two groups (total n = 116) to detect a medium effect size. This is based on using the general linear model to compare the intervention and control groups with the baseline values of an outcome measure as the covariate. It is assumed (conservatively) that the covariate would explain 10% of the variance in the dependent variable. Using data from the pilot study, the intra-cluster correlation corresponding to the schools is estimated to be 0.023, which in turn gives an estimate of 1.1 for the design effect. So in order to take account of the clustering effect of the schools, the sample size needs to be inflated to 128 (116 × 1.1).

A previous RCT conducted by the study team with a similar population had a dropout rate of 24% [60]. The proposed study differs in that the intervention will be delivered by school staff and all follow-up assessments will be conducted at school. It will also employ a shorter follow-up period, however we have estimated a dropout rate of 24% meaning that we need to recruit 169 students (128/0.76) into the study. We estimate that we can recruit about 6 students from each school, so we need to recruit 28 schools. Based on data obtained from a pilot study conducted prior to developing the RCT [39] we consider these figures to be feasible.

Every effort will be made to promote participant retention, including close liaison with school staff, maximum flexibility on the part of research staff conducting follow-up assessments, and by employing a number of methods to contact students for follow-up assessments. These will include contacting the participant via the school wellbeing coordinator in the first instance, but also by contacting them directly via phone or email and contacting them via their parents/guardians if necessary.

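### The planned test of whether staff change depends on baseline level is biased downward by regression to the mean, so its baseline coefficient cannot be read as differential gain

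*Protocol article*

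**What the plan says.** The Study design section sets a single-group comparison for staff: "The aims related to school staff will be assessed using a pre-test/post-test design". The staff aims are "4) increased confidence 5) increases in perceived skill, and 6) changes in practice among school wellbeing staff".

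Under Outcome measurements, the staff instrument is described thus: "These will be measured using a specifically designed questionnaire, based on those previously used by this research team". No reliability figure is given. There are two measurement occasions: "This will be administered prior to the beginning of each school’s involvement in the study and at the end of the intervention period".

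Under Statistical analysis, School staff outcomes, the plan has three steps: descriptive statistics, a paired t-test that "will be used to test if there is a significant change between baseline and follow-up", and a general linear model to "examine if the changes are related to possible covariates such as baseline levels and previous training". In the third step change is the dependent variable, and the baseline level of the same measure is the first-named predictor whose relation to change is to be examined.

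The student analysis differs. There, baseline is a covariate in a comparison of randomised groups, and the treatment effect is what is tested.

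**The concern.** Change contains baseline with a negative sign. If a staff member's baseline score is low by chance, the change tends to look large; if it is high by chance, the change tends to look small. A regression of change on baseline therefore has an expected slope below zero with no real dependence of gain on starting level. Testing that slope against zero tests the wrong null value.

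A control group of staff would show how much negative slope arises without the program, and a known reliability would allow a correction. The documents provide neither. What is at stake is the meaning of one secondary coefficient: a significant negative value has a ready explanation (less confident staff benefit more) that the data could not support.

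**Working it through.** **Inputs.** The protocol gives no sample size, reliability or effect figure for the staff analysis, so there is no stated figure to reproduce.

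- Number of schools, from Effect size and statistical power: "so we need to recruit 28 schools". Staff per school is not stated. Assumed: one or two, giving 28 × 1 = 28 or 28 × 2 = 56 staff.
- Significance level: the same section has "alpha is set at 0.05 and power at 0.80" for the student sample size. Assumed: two-sided 0.05 for the staff tests as well.
- Reliability ρ of the staff questionnaire is not stated. Assumed: 0.7 to 0.9.

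**Model with no differential gain.** Baseline X1 = T + e1 and follow-up X2 = T + shift + e2. Var(X1) is scaled to 1, so Var(T) = ρ and each error variance is 1 − ρ. Then:

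- Cov(X2 − X1, X1) = Cov(e2 − e1, T + e1) = −(1 − ρ)
- slope of change on baseline = ρ − 1
- Var(X2 − X1) = 2(1 − ρ)
- correlation = −(1 − ρ)/√(2(1 − ρ)) = −√((1 − ρ)/2)

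The true slope of gain on starting level is zero throughout. Simulating this model with a two-sided 0.05 test gives:

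| ρ | expected slope | expected correlation | significant negative, n = 28 | significant negative, n = 56 |
|---|---|---|---|---|
| 0.7 | −0.30 | −√0.15 = −0.39 | 55% | 85% |
| 0.8 | −0.20 | −√0.10 = −0.32 | 38% | 67% |
| 0.9 | −0.10 | −√0.05 = −0.22 | 21% | about 38% |

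The nominal rate in this direction is 2.5%. With error-free measurement the simulated rate is about 2.5%, so measurement error is the cause.

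**Gain varying between staff, unrelated to starting level.** If true gain has standard deviation s in units of the baseline SD, the covariance is unchanged but the variance of change rises. The correlation becomes −(1 − ρ)/√(2(1 − ρ) + s²). With s = 0.5:

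- ρ = 0.7: −0.30/√(0.60 + 0.25) = −0.33; significant negative results in about 41% (n = 28) and 70% (n = 56)
- ρ = 0.9: −0.10/√(0.20 + 0.25) = −0.15; about 11% and 20%

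**A real gain in the opposite direction.** If true gain rises by g per unit of true baseline, the slope is ρ(1 + g) − 1. With g = 0.2 it is 0.7 × 1.2 − 1 = −0.16 at ρ = 0.7, and 0.9 × 1.2 − 1 = +0.08 at ρ = 0.9. The downward bias is always present, but a negative result is not inevitable.

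**Previous training.** Change = a + b·baseline + c·training is the same model as follow-up = a + (1 + b)·baseline + c·training. The coefficient c is identical, and only the baseline coefficient changes.

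**Oldham's alternative (change against the mean of the two scores).** With no variation in true gain and equal variances on both occasions it rejects at about 5%. With gain SD 0.5 unrelated to baseline and ρ = 0.9, the follow-up variance exceeds the baseline variance. It then wrongly reports that high scorers gain more in about 15% (n = 28) and 28% (n = 56) of cases.

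**The case against.** Five points can be made in the plan's defence.

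- **The staff aims do not ask who gains most.** They ask whether confidence, skill and practice change, and the paired t-test of change does not use the baseline coefficient. This stands, and it limits the point to a secondary analysis.
- **The protocol draws no conclusion about low-confidence staff.** A reader might infer that the analysis will falsely show these staff gaining most, or will steer roll-out to the wrong people. The documents support neither. They state no such hypothesis, and the Discussion mentions no targeting of staff. A significant artefact is likely in some assumed settings and unlikely in others, and a negative association could be partly real.
- **Baseline in a change model is not an error in itself.** This is right where baseline is there for adjustment. It does not dispose of the point, because the text names the relation between change and baseline as something to be examined.
- **Interpretation can be left to an analysis plan that is not shown.** Much detail can be. Here, though, the protocol states the analysis, so the point concerns what it says and not what it omits.
- **The size is uncertain.** Staff numbers, reliability, equal variances and the 0.05 level are all assumed, and the simulation has a single predictor where the plan has several. This stands for the rates. The direction of the bias needs only some measurement error in the baseline score.

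**Conclusion.** The point holds as a modest one on a secondary analysis. The baseline coefficient in the staff change model is biased downward by regression to the mean. In an uncontrolled design with unstated reliability it cannot be read as differential gain.

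On the assumptions of reliability 0.7 to 0.9, 28 to 56 staff, equal variances and no variation in true gain, a spurious significant negative association arises in about 21% to 85% of cases. With gain SD of half the baseline SD, the range over the same settings is about 11% to 70%. All of these exceed the nominal 2.5% in that direction.

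The paired t-tests for the staff aims and every student analysis stand as they are, and the previous-training coefficient adjusted for baseline is the same whichever outcome is modelled. Nothing here shows that the trial will report a false finding about less confident staff; it shows only that the planned coefficient could not support such a finding.

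**What to change.** Reword the last sentence of the staff analysis so that baseline level is an adjustment covariate only. For example: the follow-up score will be modelled on previous training, adjusted for the baseline score, and the baseline coefficient will not be tested or interpreted as showing which staff gain more.

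If dependence on starting level is still to be explored, label it exploratory and state the regression-to-the-mean limitation beside the result. Oldham's method should not be prescribed as the replacement, because it is valid only if true and error variances are equal on both occasions under the null.

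The cost is a change of wording. No further data are needed.

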### Effect size and statistical power

The primary outcome of interest is changes in suicidal ideation from baseline measured at 10 and 22 weeks. This will be measured by the SIQ. No previous studies have tested the effects of an Internet-based CBT intervention on suicidal ideation, however one previous study [59] has reported moderate to large effect sizes in terms of reduced suicidal ideation, for face-to-face CBT among young people. If we assume that alpha is set at 0.05 and power at 0.80, then a sample size of 58 is required for each of the two groups (total n = 116) to detect a medium effect size. This is based on using the general linear model to compare the intervention and control groups with the baseline values of an outcome measure as the covariate. It is assumed (conservatively) that the covariate would explain 10% of the variance in the dependent variable. Using data from the pilot study, the intra-cluster correlation corresponding to the schools is estimated to be 0.023, which in turn gives an estimate of 1.1 for the design effect. So in order to take account of the clustering effect of the schools, the sample size needs to be inflated to 128 (116 × 1.1).

A previous RCT conducted by the study team with a similar population had a dropout rate of 24% [60]. The proposed study differs in that the intervention will be delivered by school staff and all follow-up assessments will be conducted at school. It will also employ a shorter follow-up period, however we have estimated a dropout rate of 24% meaning that we need to recruit 169 students (128/0.76) into the study. We estimate that we can recruit about 6 students from each school, so we need to recruit 28 schools. Based on data obtained from a pilot study conducted prior to developing the RCT [39] we consider these figures to be feasible.

Every effort will be made to promote participant retention, including close liaison with school staff, maximum flexibility on the part of research staff conducting follow-up assessments, and by employing a number of methods to contact students for follow-up assessments. These will include contacting the participant via the school wellbeing coordinator in the first instance, but also by contacting them directly via phone or email and contacting them via their parents/guardians if necessary.

### Ethics and safety

Ethical approval has been obtained from the University of Melbourne Human Research and Ethics Committee.

#### Protocols and supervision

Clear and detailed safety protocols have been developed for this study detailing how undue risk will be determined and how the research team will respond. The research assistants will receive training in the administration of the measures and in the assessment of suicide risk. The research assistant will make contact with the school wellbeing staff member once each assessment is completed. If the research assistant and the school are concerned about the participant the project coordinator will be informed and, where necessary, an immediate referral will be made to an appropriate service. Fortnightly supervision meetings with the research therapist and the clinical psychologist will be held, during which all cases will be presented and any diagnostic and/or risk issues discussed.

#### Weekly screening

In addition, participants will complete a weekly suicidal ideation screen, which will be checked by the school wellbeing staff member at the end of each session. If a participant indicates current suicidal ideation, a risk assessment will be conducted. If they are determined to be at elevated risk then the staff member will be required to follow the school’s safety protocols. They will also receive an automated email prompting them to follow these procedures.

#### Website moderation

The website will be moderated on a daily basis five days a week during the school term by the clinical psychologist and clear procedures have been established to manage any indication of risk. It will be made clear to all participants that the website will not be moderated seven days a week, 24 hours per day, therefore if urgent messages are posted on the site they may not be seen for a couple of days. The website will include information about appropriate sources of help in a crisis and participants will be encouraged to use these contacts when necessary instead of contacting the research team.

An independent safety advisory committee will oversee all safety procedures. If at any point during the trial the committee is concerned about the welfare of participants as a result of their participation in the study, they will have the capacity to suspend the trial.

All data collected will be stored securely and according to the University of Melbourne’s Policy on the Management of Research Data and Records.

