### Intervention

The Reframe-IT intervention comprises eight modules to be delivered during the 10-week intervention period. Each participant will have access to his or her own personalised webpage accessed via secure login. For safety reasons, the program will be administered in the young person’s school by the student wellbeing staff member. Once each individual module has been completed in the presence of the school staff member, participants will be able to access it from home, 24 hours a day. The program has no social networking function.

The program takes the form of an adult ‘host’ character that delivers the therapy verbally, and a series of video diaries made by young people. There are two activities per week plus homework. The site has a message board through which the participant can communicate with the research-therapist; a series of factsheets covering a range of related topics, including managing suicidal thoughts; plus downloadable relaxation MP3s. As the weeks progress additional items are added to the site, (e.g. an activity diary). Finally there is a ‘Getting help’ tab, which lists a range of local and national helplines and services that the participant can access if in crisis.

The eight modules incorporate standard CBT approaches commonly used with young people but have a specific focus on suicidal thinking and behaviours [16]: engagement and agenda setting; emotional recognition and distress tolerance; identification of negative automatic thinking; behavioural activation - help-seeking and activity scheduling (including relaxation techniques); problem solving; detecting and challenging problematic thinking, and cognitive restructuring.

Practitioner involvement will be two-fold. First, the SWC will facilitate delivery of the program (i.e. setting up appointments; managing Internet issues; and remaining in the vicinity while the participant views the program). They will also check responses to a weekly suicide screen and respond accordingly. Second, there will be involvement from the research therapist (SH) who will remain un-blinded. She will check completed activities and respond with personalised but standardised messages. She will also check the message board daily and respond accordingly.

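### The website warning to participants fits a term-time weekend but understates the wait for a message posted in a school break

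*Protocol article*

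**What the plan says.** Two sections of the protocol article bear on this.

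- **Website moderation** (under Ethics and safety) sets the schedule: moderation by the clinical psychologist "on a daily basis five days a week during the school term". It then describes what participants will be told: "the website will not be moderated seven days a week, 24 hours per day", and as a consequence "if urgent messages are posted on the site they may not be seen for a couple of days". It adds that the site carries information on sources of help in a crisis and that "participants will be encouraged to use these contacts when necessary instead of contacting the research team".
- **Intervention** describes the channel: "The site has a message board through which the participant can communicate with the research-therapist". Of the research therapist it says: "She will also check the message board daily and respond accordingly". Completed modules stay open outside school: "participants will be able to access it from home, 24 hours a day". The site also has a help tab, "which lists a range of local and national helplines and services that the participant can access if in crisis".

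The Recruitment section sets eligibility at age 14 to 18 with any suicidal ideation in the past month, and staggers entry over two years. The intervention period is 10 weeks.

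**The concern.** The moderation schedule has two limits: weekdays only, and term only. The warning reflects the first and leaves out the second. A student who relies on it would expect an urgent message to be read within about two days at any time of year. On the stated schedule that holds in term but not in a school break.

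At stake is the accuracy of a safety notice given to adolescents with recent suicidal thoughts. The other safeguards tied to school sessions, namely the nearby wellbeing staff member and the suicide screen checked at the end of each session, would be expected to pause in a break as well. That is when a correct statement of the delay is most useful. Sample size, error rates and the analysis are not involved.

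**Working it through.** **Inputs**

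- Moderation on five days a week in term (Website moderation), read as Monday to Friday.
- Warned delay of about 2 days (Website moderation).
- Break length of k whole weeks. The article gives no school calendar, so k is an assumption.

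**Term weekend (k = 0).** The unmoderated days are Saturday and Sunday, a run of 2. This reproduces the delay in the warning.

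**School break of k whole weeks.** The run contains 5k weekdays and k + 1 weekends (one before the break, and one at the end of each of its weeks):

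5k + 2(k + 1) = 7k + 2 days

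| Assumed break | Calculation | Unmoderated run |
|---|---|---|
| none (term weekend) | 7 × 0 + 2 | 2 days |
| 1 week | 7 × 1 + 2 | 9 days |
| 2 weeks | 7 × 2 + 2 | 16 days |
| 6 weeks | 7 × 6 + 2 | 44 days |

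Any break of a week or more therefore exceeds the warned delay, whatever the exact calendar.

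**Can a student be exposed to this?** The article does not confine a student's 10 weeks to a single term, and it does not say that the message board closes in breaks. Entry staggered over two years makes an overlap with a break plausible. Posting in a break is possible but not stated: the home-access sentence concerns completed modules, not the board.

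**Which schedule governs the message board?** The Intervention section's daily check carries no weekday or term limit of its own. However, the Website moderation section itself applies the idea of daily moderation to a five-day, term-only week. The Blinding and treatment fidelity section also says that the two study psychologists, one of whom is the research therapist, stay unblinded so that the site can be moderated. The natural reading is that the board check is part of that moderation and follows its schedule. The figures above use that reading.

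**The case against.** The strongest case against the point has four parts.

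1. **The notice is paraphrased.** The article summarises what participants will be told. The actual wording is not shown and may mention holidays. The Protocols and supervision section also refers to detailed safety protocols that are not shown. This stands, and it limits the point to the text as published. It does not remove the mismatch, because the schedule and the delay are both stated, in adjacent sentences.
2. **The delay is a caution, not an upper bound.** This is also right: the article sets no maximum. But a caution that names about two days, and gives only the lack of continuous cover as the reason, does not prepare a reader for 9 days or more.
3. **The programme is school-based, so term-based moderation fits it.** The schedule is a reasonable choice and is not criticised here. The point concerns only the notice, which should match the schedule.
4. **Mitigation is already in place.** Crisis contacts, the help tab and an independent safety advisory committee are all described, and the steer away from the research team applies in breaks as well as in term. This stands and is why the added risk is small.

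Two stronger readings are tempting, and the article supports neither. A reader might infer that the daily board check in the Intervention section contradicts the term-only schedule. For the reasons in the working, it is better read as a general statement that the later section makes specific. A reader might also infer that students have no cover in breaks. The article does not say so, and the safety protocols not shown may provide for it.

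**Conclusion.** The point holds as a minor one about safety wording. The described warning matches a term weekend (2 unmoderated days) and understates the wait in a school break (9 days for one week, 16 for two, on the stated schedule). It rests on three assumptions: moderation stops outside term as written, the message board accepts posts in a break, and the break lasts at least one whole week. The article does not contradict any of them, but the second is not stated and the third comes from no calendar in the article. How many students would post in a break cannot be estimated. The gain in safety from a correction is small, and the trial's result does not depend on it.

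**What to change.** Reword the notice, and the participant information if it does not already say so, to state three things: the site is not moderated at weekends or in school holidays; a message posted in the holidays may not be seen until term resumes; and the crisis contacts must be used for anything urgent. Alternatively, disable posting on the message board outside term.

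The cost is one sentence in the protocol and possibly one in the participant information. The downside is a less reassuring notice or, under the alternative, no posting in breaks. Sample size, analysis and timeline do not change.
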